### Data analysis

Data will be reviewed prior to analysis to guarantee its quality. A descriptive analysis will be performed on the characteristics (age and sex) of patients who refuse to participate in the study and the reasons for it will be described.

A descriptive analysis of each of the variables will be carried out. The mean and typical deviation will be calculated in the case of symmetric distributions, and median and interquartile ranges will be estimated if the distribution is asymmetric. For categorical data, the frequency and percentage distributions will be shown. The difference of proportions will be estimated with its relevant confidence interval of 95%.

The association of each of the independent variables with the dependent variable (adherence decrease and medication errors) will be studied, using Pearson’s Chi-square test or Fisher’s exact test (when the conditions to apply Chi-square are not satisfied) as the statistical tools to compare proportions, and the Student’s T distribution or the Mann–Whitney U non-parametric test to compare the means.

A multivariate test with a logistic regression model will be performed, using the final combined variable (adherence and medication errors) as the dependent variable, and using as independent variables those identified to be associated in the bivariate analysis. All the hypothesis testing will be performed for all analysis’, and a p < 0.05 will be accepted as significant. All the analysis methods will be adjusted considering cluster randomizations [20]. Statistical data analysis will be performed using SPSS 18.0 software.

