### Aim

The main aim of this study is to evaluate if changes of drugs with different package and/or presentation appearance for the same active ingredient are related to a decrease in adherence and an increase in usage errors, in patients ≥65 years old, undergoing chronic treatment with antihypertensives (enalapril and/or amlodipine) and hypolipidemic agents (simvastatin), over a one-year follow-up period.

The secondary objectives are: to describe the number of drug changes made at pharmacies, estimate the frequency of avoidable and non-avoidable adverse effects during the follow-up period, describe the tolerance of patients to the dispensed drugs, and study if the number of changes is related to a decrease in the degree of control of blood pressure (BP) and/or LDL cholesterol.

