### Variables

The main outcome variable is a final combined variable, defined as “having made some drug usage error and/or an inadequate adherence to treatment regimen”.

Error in drug usage is defined according to the classification proposed by Ruiz-Jarabo *et al*. [18]. The type of error will be recorded (wrong dose, wrong frequency), as well as if there was injury to the patient, in which case the type and severity will also be recorded.

Inadequate adherence will be considered if more than one forgotten dose is detected during the package counting and/or if any of the answers (Yes/No) to the 4 questions of the Morisky-Green test in its validated Spanish version [19] is wrong. In the case of discrepancies between the Morisky test and the counting, the outcome of the counting will prevail. Since one single forgotten dose is a very stringent level of accomplishment, if no adherence differences are observed, different degrees of adherence (80%, 90% and 110%) will be considered.

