**Table 1 Tab1:** **Visits and procedures to be performed**

	***Visit*** **1** ***Screening*** **(0 months)**	***Visit 2*** **(3 months)**	***Visit 3*** **(6 months)**	***Visit 4*** **(9 months)**	***Visit 5*** **(12 months)**
Recruitment following the selection criteria	X				
Informed consent	X				
Initial collection clinical information and sociodemographic data	X				
BP control	X	X	X	X	X
Lipid profile control	X		X		X
Counting of drug packages		X	X	X	X
Morisky-Green test	X	X	X	X	X
Data collection for errors and adverse effects		X	X	X	X
Collection of followed-up clinical variables		X	X	X	X

If adverse effects are detected, the notification system for adverse reactions will be followed according to standard clinical practice.

In the case that one patient does not attend a visit, at least 3 attempts to contact them by phone will be performed during different days and hours. Patients lost to follow-up and abandonments will be recorded and the reasons noted.

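### The outcome described as a fall in adherence is a status that patients can already meet at entry, and adjustment for baseline adherence is not assured

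*Protocol article*

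**What the plan says.** The Aim asks whether changes of presentation "are related to a decrease in adherence and an increase in usage errors". Sample size is likewise argued in terms of a fall in adherence, and in Data analysis the bivariate step takes each independent variable's association with "the dependent variable (adherence decrease and medication errors) will be studied".

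The Variables section defines the main outcome as "having made some drug usage error and/or an inadequate adherence to treatment regimen". The adherence part is an absolute threshold: "Inadequate adherence will be considered if more than one forgotten dose is detected during the package counting", and/or a wrong answer to any of the four Morisky-Green questions. Where the two measures disagree, the count decides: "In the case of discrepancies between the Morisky test and the counting, the outcome of the counting will prevail".

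In Table 1 the row "Morisky-Green test" is marked at all five visits, including month 0. The row "Counting of drug packages" is marked at visits 2-5 only, as is the collection of errors and adverse effects.

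The logistic model is fitted "using the final combined variable (adherence and medication errors) as the dependent variable", with covariates chosen by bivariate association. The variable list under Secondary outcome variables does not name baseline adherence, although it gives first-to-last differences for blood pressure and body mass index. The Patients section requires a stable dose for three months but not adherence at entry. The Discussion states that the exposure cannot be randomised.

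**The concern.** A decrease is a change from a starting point; the defined outcome is a state during follow-up. The Sample size section assumes 50% adherence in patients on chronic treatment. On that figure about half the cohort could meet the adherence part of the outcome on the day they enter. The outcome alone cannot separate these patients from those who became non-adherent after a change of presentation. The definition also does not say whether visit-1 Morisky-Green answers count. If they do, some events precede the exposure.

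The second issue is confounding. A change of presentation can happen only when a pack is dispensed, so patients who collect fewer packs have fewer chances of being exposed. Earlier adherence may thus be related to both exposure and outcome. If it is left out of the model, the odds ratio for presentation changes, which is the result the study exists to produce, can be biased.

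**Working it through.** **1. Texts side by side**

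| Element | Reference to entry? |
|---|---|
| Aim | Yes, a decrease |
| Sample size | Yes, a decrease event |
| Bivariate step | Yes, a decrease |
| Outcome definition (Variables) | No, an absolute status |
| Dependent variable of the logistic model | No, the combined status variable |
| Morisky-Green at visit 1 (Table 1) | Collected; role in outcome and model not stated |
| Package count (Table 1) | No value at visit 1 |

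The protocol gives no figure for the effect of baseline adherence, so there is none to reproduce. What follows is an illustration.

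**2. Inputs**

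- From the protocol: 50% adherence, hence 50% non-adherent at entry; planned odds ratio 2.
- Assumed, with no source in the protocol: 9 packs a year if non-adherent at entry and 12 if adherent; chance r of a change per pack of 5%, 8% or 12%; outcome risk without exposure of 70% if non-adherent at entry and 30% if adherent.

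**3. Exposure probability**, 1 - (1 - r)^packs

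| r | Non-adherent at entry (9 packs) | Adherent at entry (12 packs) |
|---|---|---|
| 0.05 | 0.370 | 0.460 |
| 0.08 | 0.528 | 0.632 |
| 0.12 | 0.684 | 0.784 |

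**4. Share non-adherent at entry in each exposure group.** For r = 0.05:

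- exposed: 0.370 / (0.370 + 0.460) = 0.446
- unexposed: 0.630 / (0.630 + 0.540) = 0.538

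**5. Crude odds ratio with no true effect** (r = 0.05)

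- exposed risk: 0.446 × 0.70 + 0.554 × 0.30 = 0.478
- unexposed risk: 0.538 × 0.70 + 0.462 × 0.30 = 0.515
- odds ratio: (0.478/0.522) / (0.515/0.485) = 0.86

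The same steps give 0.84 at r = 0.08 and 0.81 at r = 0.12.

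**6. Crude odds ratio when the odds ratio within each baseline stratum is 2.** Doubling the odds turns a risk of 0.70 into 0.824 and 0.30 into 0.462. For r = 0.05 the exposed risk is 0.446 × 0.824 + 0.554 × 0.462 = 0.623, against 0.515 unexposed, giving an odds ratio of 1.55. At r = 0.08 it is 1.52 and at r = 0.12 it is 1.46.

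**7. How much of that is confounding?** With equal exposure in both strata there is no confounding. The risks are then (0.824 + 0.462)/2 = 0.643 and (0.70 + 0.30)/2 = 0.50, an odds ratio of 1.80. So 2 to 1.80 is non-collapsibility of the odds ratio, and only 1.80 to 1.46-1.55 is confounding.

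**8. Opposite imbalance, no true effect.** Suppose 60% of patients non-adherent at entry and 40% of adherent patients are exposed. The risks are 0.60 × 0.70 + 0.40 × 0.30 = 0.54 and 0.40 × 0.70 + 0.60 × 0.30 = 0.46, an odds ratio of 1.38. With exposure 65% versus 35% and outcome risk 80% versus 20%, the risks are 0.59 and 0.41 and the odds ratio is 2.07, about the planned effect.

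**The case against.** A reader might infer that the baseline is ignored and that prior non-adherence is an uncontrolled confounder. The text does not go that far. Nothing says the visit-1 value is discarded, and a journal article may leave the full list of candidate covariates to the full protocol. If visit-1 Morisky-Green were offered to the bivariate screen, it would very likely be selected whenever it predicts the outcome strongly. This stands: the fault is that control is not assured. It remains a fault of the stated rule, because that rule makes adjustment for an obvious baseline variable depend on a significance test.

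A reader might also infer that the bias runs towards no effect, or that confounding alone takes an odds ratio of 2 down to about 1.5. Neither is supported. The refill pattern, the change rate and the outcome risks are assumptions, and reversing the exposure imbalance reverses the bias. Even under the refill assumption, the no-effect result moves away from 1, in the protective direction. Part of the fall from 2 is non-collapsibility, and the planned odds ratio is stated as a group comparison, not as conditional on baseline adherence.

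Finally, the remedy is imperfect. The prevailing measure, the package count, has no value at visit 1, so adjustment for Morisky-Green is partial. For the same reason, restricting to patients adequate on Morisky-Green at visit 1 does not isolate a true decrease. This also stands.

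**Conclusion.** The point holds in a limited form. The mismatch between a decrease and a status is in the current text and depends on no assumption. So is the silence on whether visit-1 answers count, and so is the absence of any commitment to adjust for baseline adherence in a non-randomised comparison. That baseline adherence confounds the result is plausible through refill frequency but is not shown by the protocol.

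Under the assumed inputs the confounding part is moderate: a crude odds ratio of 0.81-0.86 where the truth is 1, and 1.46-1.55 where 1.80 would be expected without confounding. Other assumed imbalances give 1.38 to 2.07 with no effect at all. The direction is uncertain, but the possible size matters against a planned odds ratio of 2. The change should be made because it needs no new data.

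**What to change.** 1. In Variables, state that outcome events are counted from visits 2-5 only.
2. In Data analysis, enter visit-1 Morisky-Green (0-4 score, or adequate/inadequate) in the primary logistic model regardless of the bivariate screen.
3. In the Aim, Sample size and Data analysis, describe the outcome as inadequate adherence or usage error during follow-up, adjusted for baseline adherence, in place of a decrease.
4. Optionally, add a sensitivity analysis in patients adequate on Morisky-Green at visit 1. At the plan's 50% figure this leaves about 120 of the 240 patients required before the allowance for losses (240 × 0.5), and it only approximates new non-adherence because package counts start at visit 2.

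The cost is one more model term and no extra data collection. Adjustment stays partial, since the count that prevails has no baseline value, and the report should say so.

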**Methods/Design:**

We propose a multicentric observational longitudinal cohort study with a one-year follow-up period in 8 primary health care centers (PHCC) in the Community of Madrid. 259 patients who are ≥65 years old, hypertensive and/or dyslipidemic, undergoing treatment with enalapril and/or amlodipine and/or simvastatin, and under formal follow-up of chronic patients in primary health care will be selected by simple random sampling. The main outcome variable will be a final combined variable (adherence and medication usage errors). Other included variables will be: sociodemographic and clinical variables of the patient, degree of disease control, drug taken, number of changes in the appearance of each drug by the pharmacy, and the type and frequency of both avoidable and non-avoidable adverse effects during the follow-up period. A descriptive and a multivariate analysis of the variables will be carried out by means of a logistic regression model, using the final combined variable as the dependent variable (error and/or inadequate usage of the drug), and variables shown to be related to it during the bivariate analysis as the independent variables.

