### Secondary outcome variables

#### Sociodemographic

Age, sex, level of education (illiterate, without studies, primary studies, secondary studies, superior education), and PHCC.

Related to the prescription and active ingredient:Prescribed active ingredient: enalapril, amlodipine, or simvastatin.Change of drug presentation at the pharmacy (Yes/No).Number of changes per drug.Suffering an adverse reaction to the drug (Yes/No), interruption of medication (Yes/No), and the reason for such interruption.Number of avoidable and non-avoidable adverse effects during the follow-up period.Tolerance of the patients to the dispensed drugs according to their own direct statement.

Clinical and analytical:Years of development of HTN and/or dyslipidemia. Presence of pathologies that modify the HTN (nephropathologies, sleep apnea, obesity, and malnutrition). Presence of pathologies that modify the lipid profile (hyperthyroidism, hypothyroidism, obesity, and malnutrition). Comorbidity (cardiovascular pathology, neurological pathology).Treatments that modify BP and the lipid profile (diuretics, alpha and beta blockers), anti-inflammatories, antidepressants and anxiolytics, thyroxin, hormone replacement therapy. Other concomitant treatments.Figures of systolic blood pressure (SBP) and diastolic blood pressure (DBP) in each visit. Difference of SBP and DBP between the first visit and the last recorded data. Percentage of patients with good control at the beginning and at the end of the study.Total HDL cholesterol, LDL cholesterol, and triglycerides, both initial and after one year.Initial and final weight. Initial height. Difference in body mass index (BMI) between the first and final visits.

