## Discussion

In our environment, the effects that new legislative measures related to drug prescription may have on the safety of the patient are unknown. For chronic treatment, the interchangeability of drugs with different package appearances and presentations for the same active ingredient may lead to mistakes when choosing the package, or to dose duplications, as well as affecting adherence to treatment by not taking or inadequately taking the medication. These errors may be much more frequent in more vulnerable populations, such as elderly or multi-medicated patients.

Patients will be included and monitored in the study by their own primary care doctors according to standard practice. Including patients from different health professionals implies an increase of variability on the one hand, but on the other hand guarantees a lower number of losses to follow-up since they are chronic patients over 65 years old who periodically attend the PHCC, therefore enabling the analysis of the outcome under conditions of real clinical practice.

It must be highlighted that, in Spain, the majority of the population with the most prevalent chronic pathologies, such as HTN and dyslipidemia, is attended and supervised in primary health care.

In order to decrease the variability among health professionals, training sessions will be held and the protocol for the follow-up of hypertensive patients in primary health care in Madrid will be respected, having been implemented in the data collection notebook. Homologated, calibrated blood pressure meters will be used in order to guarantee the reliability of BP measurements.

We consider that despite the limitations that an observational study may have for answering our question, namely the lack of feasibility of performing a clinical trial as a result of not being able to randomize the intervention (interchangeability of drugs at the pharmacy), it will provide information on the possible effects that the recent legislative changes may have on patient safety.

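### The logistic model admits only variables that pass a bivariate significance test and exempts neither the exposure nor any confounder, so the adjusted odds ratio can be missing, overstated or under-adjusted

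*Protocol article*

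**What the plan says.** The Aim section sets one main task: "evaluate if changes of drugs with different package and/or presentation appearance for the same active ingredient are related to a decrease in adherence". Usage errors form the other half of the outcome. This is a question about one exposure. The Discussion acknowledges that this exposure cannot be randomised.

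The Data analysis section proceeds in two steps. First, "The association of each of the independent variables with the dependent variable" is tested, by chi-square or Fisher's exact test for proportions and by the t-test or Mann–Whitney test for means. Then a logistic model is fitted to the combined outcome, "using as independent variables those identified to be associated in the bivariate analysis". For all hypothesis tests, "a p < 0.05 will be accepted as significant". The Abstract (Methods/Design) gives the same rule: the model takes "variables shown to be related to it during the bivariate analysis as the independent variables".

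The yes/no change of presentation and the "Number of changes per drug" appear under Secondary outcome variables, in one list with the other recorded items. Nothing gives them a reserved place in the model, and no confounder is named for adjustment in advance.

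The Data analysis section also plans a difference of proportions with a 95% confidence interval, and adjustment of all analyses for clustering.

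**The concern.** In an observational study of one exposure, the multivariable model is there to separate that exposure from confounding. Confounding depends on a variable's relation to both exposure and outcome. The screen looks only at the crude p-value against the outcome, so it can go wrong in three ways:

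- The exposure may fail the screen, and then no adjusted estimate exists. Where a confounder hides the effect, this is the case in which adjustment is most needed.
- If the exposure is reported only when its crude test is significant, the reported OR is selected for being large.
- A real confounder may fail the screen because the sample is modest, and the exposure OR is then left under-adjusted.

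The adjusted OR for presentation change is at stake, which is the estimate closest to the study's main question. The rule is stated twice, so it is a fixed choice and not a detail left to an unseen analysis plan.

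**Working it through.** **Inputs from the protocol (Sample size).** 50% adherence; OR 2 for exposed against non-exposed; alpha 0.05; beta 0.20; 237 patients before adjustment, 240 after clustering, 259 after 7% loss. A 20-point difference is also stated.

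**Assumed, because not stated.** A 1:1 split of exposed to non-exposed; a two-sided test; p < 0.05 as the entry criterion; all confounder strengths below.

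**The plan's own figures.** 240 / (1 − 0.07) = 258.1, rounded up to 259, so about 240 evaluable patients is the right basis. The 237 is nearly reproduced (238) with 50% against 66.7%, a one-sided test and a continuity correction. A two-sided test without correction needs 274. That is why two-sided power below is under 80%.

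**Chance that the exposure fails the screen, no confounding.**
- OR 2 from 50%: odds 1 × 2 = 2, so the risk is 2/3 and the difference 0.1667. With 120 per group the pooled risk is 0.5833.
- Null standard error: √(2 × 0.5833 × 0.4167 / 120) = 0.0636.
- Alternative standard error: √((0.25 + 0.2222) / 120) = 0.0627.
- z = (0.1667 − 1.96 × 0.0636) / 0.0627 = 0.67, so power is 0.748 and the exposure fails in about 25% of samples.

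Sensitivity of that 25%:
- Split of 3:1 to 4:1 in either direction: 37% to 45%.
- Planned design effect 1 + 14 × 0.01 = 1.14, effective size 240 / 1.14 = 210.5: power 0.691, fails in 31%.
- 50% against 70% (the stated 20 points): power 0.890, fails in 11%.
- True OR 1.5 (simulated): fails in 66%.

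**Simulation of the full rule.** 240 patients, binary exposure and one binary confounder, no clustering, 4,000 replicates per scenario. The screened analysis applies a chi-square test at p < 0.05 to each variable and then fits a logistic model with those that pass. The forced analysis always includes both. Mean ORs are on the log scale.

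| True OR | Confounder OR with outcome / exposure | Exposure dropped | Confounder dropped | Mean OR, forced | Mean OR when kept by screen | Power, forced | Power, screened |
|---|---|---|---|---|---|---|---|
| 2 | none | 25% | – | 2.01 | 2.24 | 75% | 74% |
| 1.5 | none | 66% | – | 1.52 | 2.01 | 34% | 34% |
| 2 | 0.5 / 2.5 (masking) | 49% | 49% | 2.02 | 2.30 | 72% | 51% |
| 2 | 1.5 / 2.5 (same direction) | 16% | 45% | 2.01 | 2.20 | 74% | 77% |
| 1 | 1.6 / 4 (same direction) | 91% | 56% | 1.00 | 1.57 | 5.1% | 4.6% |

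In the last row, power is the false-positive rate in the final model. A second run of rows 1, 3, 4 and 5 had 2,500 replicates, exposure and confounder each in half of patients, and 50% average outcome risk in the unexposed. It agreed within 3 percentage points and 0.05 in the OR.

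**Reading the table.** Without confounding, the screen costs almost no power (75% against 74%). It costs the estimate in a quarter of samples and inflates it in the rest. With a masking confounder it also costs about 21 points of power. With confounding in the same direction as the effect, power is not lost, but the confounder is dropped in about half of samples and the kept OR is too high. In the null row the harm lies in the estimate, not in the false-positive rate.

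**The case against.** Several points on the other side stand.

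- **Screening of the exposure is inferred.** The text never says that the exposure is removed if non-significant. The reading follows from the test being applied to each independent variable and from the absence of any exemption. If the authors always intended to keep it, one sentence settles that part, but the screen on confounders remains.
- **The 25% is not power lost to the screen.** A reader might infer that the rule makes the study miss a true effect a quarter of the time. Without confounding, a forced model would be non-significant about as often.
- **The study would not be left without any estimate.** A difference of proportions with its 95% interval is still planned, although it is unadjusted.
- **The 21-point power loss belongs to one assumed direction.** Nothing in the protocol says that confounding masks the effect. The Background and Discussion single out older, multi-medicated patients as vulnerable, and such patients may plausibly see more changes, not fewer. That would be confounding in the same direction as the effect.

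A reader might also infer that the screen leaves out an obvious confounder, the number of study drugs: patients on two or three drugs have more chances both of a change and of an error. Under assumed drug mixes and per-drug risks, ignoring it does give a spurious OR of about 1.3 to 1.6. That figure is the bias of an unadjusted OR, not of this rule. In those same scenarios the drug count passes a p < 0.05 screen in 87% to nearly 100% of samples, depending on the test. The count can also be derived from the recorded active ingredients. It is a sensible adjustment variable, but not evidence against the screen.

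**Conclusion.** The concern holds in a bounded form. The rule is explicit, is stated in two places, and does not suit a non-randomised study of one exposure. As written it can leave no adjusted OR for the main question, overstate the OR that is reported, and omit confounders that are real but not individually significant.

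The failure rate of about 25% at OR 2 rests on 240 patients and the assumed 1:1 split. It ranges from 11% to 45% over the other planned effect size, clustering and unequal splits. The overstatement (about 2.24 for a true 2) needs no confounding at all. The drop from 72% to about 51% power, and the dropping of each variable in about half of samples, depend on the assumed masking confounder. The documents do not support a general claim that the rule loses power, or that confounders are always omitted.

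**What to change.** In the Data analysis section and the Abstract:

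1. State that the presentation-change variable is always in the logistic model, whatever its bivariate result.
2. Replace the p-value screen by a short adjustment set, named in advance on subject-matter grounds. Candidates already collected or derivable are age, sex, education, comorbidity, number of study drugs, number of concomitant drugs and the baseline Morisky-Green result (Table 1, visit 1). The exact list is for the investigators to choose; what matters is that it is fixed beforehand.
3. Keep the planned adjustment for clustering, by doctor.
4. Keep the bivariate tables as description only.

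The cost is wording, with no new data and no extra patients. The downside is degrees of freedom. Exposure 1, age 1, sex 1, comorbidity 2, study drugs 1, concomitant drugs 1 and baseline adherence 1 make 8. Education adds 2 if collapsed to three levels (10) or 4 with its five levels (12), and coding the number of study drugs as categories makes 13. At the planned risks the rarer outcome class has about 240 × 0.4167 = 100 patients, so 100 / 10 = 10 to 100 / 13 = 7.7 per degree of freedom. That is workable but argues for a short list, and more so if adding usage errors to the outcome makes that class smaller.
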